**Methods/Design:**

In an open label non-randomized trial treatment with baclofen to a maximum of 60 mg/day will be compared with treatment as usual (TAU) in recently detoxified GHB dependent patients (n = 80). The primary outcome measure will be the level of GHB use. Secondary outcome measures are craving levels, psychiatric symptom levels and quality of life. Questionnaires will be administered during 12 weeks of baclofen treatment and at follow-up (six months after the start of treatment).

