### Study intervention

#### Baclofen intervention

Clinical trials on baclofen for alcohol dependence treatment have used baclofen at a dose of 30 mg ⁄d [29-31] over 30 to 120 days. This is within the low therapeutic range for muscle spasms. However, Garbutt and colleague’s [32] suggested that 30 mg of baclofen per day may be an insufficient dose for some patients to achieve abstinence. Additionally, baclofen effectiveness for GHB dependence could be smaller, since tolerance may occur due to recent abuse of GHB and a possible substitution function (as treatment will be started immediately after detoxification).

Based on these results and the unpublished results of a small dose finding experimental treatment study in our treatment center, where patients reported limited effect of baclofen 30 mg per day, we decided to administrate a dose of 45 mg to a maximal dose of 60 mg per day orally to avoid the risk of (co) intoxication. In this study baclofen will be administrated orally three times daily as usually recommended [22] and started with a total dose of 15 mg per day. During the first 10 days baclofen will be gradually increased with 15 mg per day every 3 days up to the chosen minimum dose of 45 mg, or a maximum dose of 60 mg in case no effect is reported at 45 mg after 2 weeks. This dose will subsequently be maintained for a period of 10 weeks. Successively, baclofen will be tapered off to 0 mg in 2 weeks (see Table 1). Patients will be asked to avoid abrupt termination of baclofen and will be guided by their physician to avoid complications of baclofen withdrawal. Patients who wished to continue the baclofen treatment will be offered an outpatient counselling and medication by their physician for another 3 months.

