#### Additional measures

Addiction physicians will be asked to monitor withdrawal symptoms when tapering baclofen, using standard questions. These include a short check of the most reported withdrawal symptoms in the literature [43,44].

We will monitor the use of other substances over the last thirty days (number of days and quantity) using section 1 of the Measurement of Addicts for Triage and Evaluation (MATE) before and after detoxification and at follow up (3 months). The MATE is a Dutch instrument designed as an aid in the diagnosis of clinically relevant patient characteristics in substance use disorders according to the DSM-IV axes [45].

At 6 month period we will also report on the needed period of treatment with baclofen to maintain abstinence by monitoring relapse (Timeline Follow back) and craving assessment (DDQ, VAS) within the intervention group between those who used baclofen for 3 month only and those who choose to continue the treatment further.

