### Procedure and data collection

Patients in all treatment conditions (baclofen + TAU or TAU only) will be assessed by research assistants identically in the following time points. Before detoxification, the intensity of GHB abuse (MATE), Quality of life (EQ-5D) and psychiatric comorbidity (DASS) will be assessed. At the end of the detoxification treatment (baseline) and at follow up (three months after start of detoxification) craving (VAS, DDQ), psychiatric comorbidity (MINI plus, DASS), and Quality of life (EQ-5D) will be assessed.

The addiction physician will monitor the participants in the baclofen condition during regular medical check-ups for potential side effects (side effect checklist) and craving (VAS, DDQ), see Table 2. During the follow-up (six months after start of detoxification) the DDQ, DASS, MINI-plus, EQ-5D will be repeated. In summery self-report questionnaires will be administered at the start of detoxification; start of baclofen treatment (week 0), baclofen titration and stabilization (week 1 + 2) and maintenance treatment (week 3–12). Add to that, three months after the end of the baclofen treatment, a follow-up measurements will take place. The research assistant will build up an online Client Record Form from all the questionnaires filled in by the patients. A summary of the medical records will be added by the physician to the electronic patient file.

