**Table 2 Tab2:** **Time measurements**

**Week**	**0**	**1**	**2**	**3**	**4**	**5**	**6**	**7**	**8**	**9**	**10**	**11**	**12**	**13**	**14**	**15**	**24**
Measurement	**T0**-baseline	**T1**											**T2**				**T3**
Mate section	xx												xx				x
EQ–5D	xx												xx				x
DASS	xx												xx				x
Mini-plus	xx												xx				x
Blood	xx						x						x				
Urine	xx						x						xx				x
Medical consult	2x	2x	2x	x	x			x			x		x	x	x		
Baclofen (mg)	0	15–30	45– 60											30–45	30–15	15–0	0
Baclofen Side effect	x	2x	2x	x	x			x			x		x				
VAS	xx	x	x	x	x			x			x		xx				x
DDQ	xx	x	x	x	x			x			x		xx				x
Baclofen withdrawal checklist														x	x	x	
Timeline follow back													xx				x

xx = baclofen group and control group TAU only.

x = baclofen group.

T0 = end of GHB detoxification.

T1 = start baclofen treatment.

T2 = follow-up TAU only and end of baclofen therapy.

T3 = follow-up baclofen group.

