### Statistical analyses

Descriptive analysis will be executed for all measurements and will include the mean, SD and frequencies of events with confidence intervals. Descriptive statistics will be used to compare the basic characteristics of the participants in the experimental group and the control groups. To assess any difference in relapse rates between the experimental group and the control groups (TAU group and matched historical group) at 3 month after detoxification Pearson Chi-squared test will be used for the dichotomous abstinence rates. ANOVA will be carried out on continuous variables, such as the total number of abstinent days, the maximum duration of continued abstinence, time before relapse (relapse defined as ≥ 3 times GHB use per day, for 2 subsequent days), and level of substance use over a period of 3 months. At 6 months period participants who continued baclofen will be compared to those who have stopped with baclofen (after 3 month) on relapse into GHB abuse or abstinence corrected for craving. The numbers of patients maintaining abstinence will be analysed with the intention-to-treat principles. The difference in craving will be analysed by MANCOVA at 3 months between groups (abstinent experimental versus abstinent TAU or relapsed TAU) with DDQ and VAS craving as dependent variables and corrected for craving levels immediately after detoxification. The change in craving in time during the baclofen treatment will be analysed via repeated measures MANOVA. By means of MANCOVA at 6 months after detoxification the difference in craving among participants who are still using baclofen and those who have discontinued baclofen will be analysed corrected for craving after 3 months. The effect of baclofen on the psychiatric symptoms levels (DASS, MINI) and also quality of life (EQ–5D) will be analyzed similarly as for craving at 3 and 6 months. The effects of the different TAU approaches as potential confounders will be tested in a sensitivity analyses (changing one-factor-at-a-time) in an linear regression including TAU per center as covariates.

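### The six-month comparison of patients who continue and patients who stop baclofen cannot give the required duration of treatment that the protocol says it will report (minor)

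*Protocol article*

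**What the plan says.** Four parts of the protocol article bear on this point.

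- **Additional measures** sets the deliverable: at six months, "we will also report on the needed period of treatment with baclofen to maintain abstinence". The evidence is to come from relapse and craving within the intervention group, compared between "those who used baclofen for 3 month only and those who choose to continue the treatment further".
- **Baclofen intervention** describes the extension. Patients who wish to go on after the standard course "will be offered an outpatient counselling and medication by their physician for another 3 months".
- **Table 2** places the last assessment, T3, in week 24 ("T3 = follow-up baclofen group"). It schedules nothing later. Its baclofen row shows 0 mg in week 24, without an exception for continuers.
- **Statistical analyses** gives two six-month contrasts. For relapse: "At 6 months period participants who continued baclofen will be compared to those who have stopped with baclofen (after 3 month". For craving, the groups are "participants who are still using baclofen and those who have discontinued baclofen".

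Procedure and data collection dates the follow-up in two ways. One sentence reads "During the follow-up (six months after start of detoxification) the DDQ, DASS, MINI-plus, EQ-5D will be repeated". A later sentence puts a follow-up three months after baclofen treatment ends.

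**The concern.** Whether a course was long enough to maintain abstinence shows only once the course is over. At week 24 one group has been off baclofen for some time, while the other, if it completes the extension, is still taking it or only just finishing. The contrast is therefore mainly on-drug against off-drug, not a six-month course against a three-month course.

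The rival explanation is one the protocol raises itself. The Background suggests that baclofen may act as a substitute for GHB, and the Discussion says the study wants to test that idea. Under substitution, use is held back while the drug is taken and may return after it stops, whatever the length of the course. Continuers would then do better at week 24 although no longer course had been shown to be needed.

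At stake is what the trial may conclude. Better results in continuers could be put forward as an answer to the duration question when they are not one.

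**Working it through.** The plan gives no figure for this comparison. Its sample size covers only baclofen plus usual treatment against control. The check is on the timeline and on what the week-24 data can tell apart.

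**Inputs**
- Last assessment: week 24 (Table 2).
- End of maintenance: week 12. End of taper: week 15 (Tables 1 and 2).
- Extension: three further months (Baclofen intervention). I take this as 12 weeks (3 × 4) or 13 weeks (a calendar quarter).
- Start of the extension: not stated. I take week 12 or week 15.

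**Stoppers.** Drug-free weeks at T3 = 24 − 15 = 9. The text under Baclofen intervention gives a two-week taper where Tables 1 and 2 show three weeks. On the two-week reading the figure is 24 − 14 = 10.

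**Continuers who complete the extension.** End week = start + length, before any taper.

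| Extension starts | Length | Ends in week | Drug-free weeks at week 24 |
|---|---|---|---|
| week 12 | 12 weeks | 24 | 0 |
| week 12 | 13 weeks | 25 | 0 (1 week of treatment left) |
| week 15 | 12 weeks | 27 | 0 (3 weeks left) |
| week 15 | 13 weeks | 28 | 0 (4 weeks left) |

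On all four readings, completers have no drug-free time at T3, against about 9 weeks for stoppers.

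**If six months means 26 weeks (2 × 13) from the start of treatment.** Only the week-12 starts would leave any drug-free time: 26 − 24 = 2 weeks or 26 − 25 = 1 week, again before any taper. Stoppers would have 26 − 15 = 11 weeks. The imbalance remains.

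**Continuers who stop early.** A patient who goes on past week 15 and takes the last dose in, say, week 18 has 24 − 18 = 6 drug-free weeks at T3. By the wording for relapse this patient continued; by the wording for craving this patient has discontinued. The two contrasts therefore need not have the same groups, and no analysis by actual duration or by time since last dose is described.

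**What week 24 can tell apart.** Take two possible truths.
1. *Suppression only:* stoppers relapse after their taper. Continuers are abstinent at week 24 and relapse after their own last dose.
2. *Longer course needed:* stoppers relapse after their taper. Continuers are abstinent at week 24 and stay abstinent after their own last dose.

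The two agree on everything seen up to week 24. They differ only after the extension ends, at about week 24 to 28, and Table 2 has no visit there. The planned corrections for craving do not help, because no adjustment supplies off-drug observation that was not collected. For the same reason, random allocation to continue or stop would not remove this problem.

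**The case against.** The strongest case on the other side has five parts.

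1. *The three-month course is observed after it ends.* This stands. If stoppers remain abstinent about 9 weeks after the taper, that bears on whether about three months was enough. The evidence is weak, because patients choose their group and because relapse can itself end treatment: the text after Table 1 says stopping will be considered, while the Discussion says it will be immediate. A reader might infer that week 24 says nothing at all about duration; the documents do not support that.

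2. *The aim may only ask whether treatment must go on past three months for abstinence to hold.* On that reading the contrast is relevant as a description of continued against stopped treatment. It still does not yield a length of treatment.

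3. *Not every continuer need be on drug at week 24.* This stands. The extension is an offer, and nothing says that everyone completes it. A reader might infer zero drug-free weeks for every continuer, or that only two durations will occur. Neither is established; the zero holds for those who complete the extension.

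4. *A later observation may be intended.* Procedure and data collection mentions a follow-up three months after baclofen ends. Counted from each patient's own last dose, it would show continuers off drug. But Table 2 has no such visit and the analysis is set at six months. Counted from week 12, the sentence gives 12 + 12 = 24, which is T3 for patients on the standard course. That is the likelier meaning, but the text leaves it open, so a flat statement that nothing later is planned would go too far.

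5. *The protocol never says that a difference will be read as a need for longer treatment.* True. It also calls the study explorative and leaves firm conclusions to later randomised trials. This lowers the severity, but it does not justify naming an output that the data cannot give.

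**Conclusion.** The point holds in a limited form. For continuers who complete the extension, the six-month contrast sets patients on drug, or just finishing, against patients about 9 weeks off it. It can describe relapse and craving under continued and stopped treatment. It cannot separate suppression of use during treatment from a need for a longer course, and so it cannot give a required duration.

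This rests on three assumptions: the extension runs 12 to 13 weeks from week 12 or week 15, T3 is at about week 24, and no off-drug visit for continuers exists beyond Table 2. How many continuers will complete the extension is unknown.

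Severity is minor. The claim is one sentence under Additional measures. It is not part of the stated aims and hypotheses, the between-group comparison of relapse or the sample size.

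**What to change.** **Reword the deliverable.** In Additional measures, drop the claim to report the required duration, and bring the six-month contrasts in Statistical analyses into line. Suggested text: *At week 24, GHB use and craving will be described, as an exploratory comparison, in patients who continued and patients who stopped baclofen after the standard course. Actual treatment duration and time since last dose will be reported for each group. No conclusion will be drawn on the duration of treatment required.* Use one definition of the two groups for both relapse and craving.

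**Reconcile the schedule.** State whether the follow-up three months after baclofen ends, in Procedure and data collection, refers to the standard course or to each patient's own last dose. Make that sentence and the 0 mg entry for week 24 in Table 2 agree with the extension under Baclofen intervention.

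**An extra contact is not needed.** One could think of a Timeline Follow-back call to continuers about 9 weeks after their last dose, at about week 33 to 37 (24 + 9 to 28 + 9). It would equalise drug-free time but not remove selection: since relapse can end treatment, patients who reach the end of the extension are already selected for staying abstinent.

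**Cost.** Edits to the text, and a recorded date of last dose for each baclofen patient. No added visits and no change to treatment.

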### Procedure and data collection

Patients in all treatment conditions (baclofen + TAU or TAU only) will be assessed by research assistants identically in the following time points. Before detoxification, the intensity of GHB abuse (MATE), Quality of life (EQ-5D) and psychiatric comorbidity (DASS) will be assessed. At the end of the detoxification treatment (baseline) and at follow up (three months after start of detoxification) craving (VAS, DDQ), psychiatric comorbidity (MINI plus, DASS), and Quality of life (EQ-5D) will be assessed.

The addiction physician will monitor the participants in the baclofen condition during regular medical check-ups for potential side effects (side effect checklist) and craving (VAS, DDQ), see Table 2. During the follow-up (six months after start of detoxification) the DDQ, DASS, MINI-plus, EQ-5D will be repeated. In summery self-report questionnaires will be administered at the start of detoxification; start of baclofen treatment (week 0), baclofen titration and stabilization (week 1 + 2) and maintenance treatment (week 3–12). Add to that, three months after the end of the baclofen treatment, a follow-up measurements will take place. The research assistant will build up an online Client Record Form from all the questionnaires filled in by the patients. A summary of the medical records will be added by the physician to the electronic patient file.

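### The 3-month visit that collects the primary outcome is timed from the start of detoxification in one section and from its end in others, and the final follow-up has four origins

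*Protocol article*

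**What the plan says.** **3-month point.** The Procedure and data collection section places the assessment "at follow up (three months after start of detoxification". The Statistical analyses section states that "at 3 month after detoxification Pearson Chi-squared test will be used for the dichotomous abstinence rates". The legend of Table 2 has "T0 = end of GHB detoxification", with T2 in the week-12 column. The sample size section takes its 36% control rate over 3 months counted after detoxification. The primary outcome section names 3 and 6 months without an origin, but counts continued abstinence from after detoxification.

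**Where the primary data come from.** Table 2 marks the Timeline Follow-back at week 12 for both the baclofen and TAU-only groups, and at week 24 for the baclofen group only.

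**Final follow-up.** Four origins appear:
- Abstract: "at follow-up (six months after the start of treatment".
- Procedure section: "During the follow-up (six months after start of detoxification) the DDQ, DASS, MINI-plus, EQ-5D will be repeated".
- Statistical analyses: "By means of MANCOVA at 6 months after detoxification the difference in craving".
- Procedure section again, a few sentences after the first: "three months after the end of the baclofen treatment, a follow-up measurements will take place".

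**End of baclofen.** The Table 2 legend ties T2 (week 12) to the end of the baclofen course, and the abstract speaks of 12 weeks of treatment. The dosing rows of Tables 1 and 2 run through week 15.

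**The concern.** The number of abstinent days, the duration of abstinence and the proportion abstinent all depend on how long patients are observed after detoxification. The Timeline Follow-back looks backwards, so it cannot cover days after the interview. If a centre dates the 3-month visit by the Procedure section, the detoxification period uses up part of the three months and the interview comes too early for the analysis that is planned. For baclofen patients the week-24 interview might recover those days. For TAU-only patients nothing can.

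The matched historical group is the second comparator, and its rate is for 3 months after detoxification. Current patients observed for less time than that would look more often abstinent for a reason unrelated to baclofen.

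**Working it through.** **1. The plan's own figure.** With 70% against 36%, the stated formula gives (1.96 + 0.84)² × (0.70 × 0.30 + 0.36 × 0.64) / 0.34² = 29.87, so 30 per group. Allowing for 25% dropout, 30 / 0.75 = 40. Both agree with the article, and this point does not touch the sample size.

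**2. Loss of window at 3 months.** Table 2 treats 3 months as 12 weeks, or 84 days. If the visit is counted from the start of detoxification and detoxification lasts d days, the window after detoxification is 84 − d days. The documents do not give d, so these values are assumptions:

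| Assumed d (days) | Window (days) | Loss |
|---|---|---|
| 7 | 77 | 8% |
| 14 | 70 | 17% |
| 28 | 56 | 33% |

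**3. Effect on the abstinence rate.** Assume a constant relapse hazard giving 36% abstinent at 12 weeks. At t weeks the proportion is 0.36^(t/12).
- 11 weeks: 0.36^(11/12) = 0.392.
- 10 weeks: 0.36^(10/12) = 0.427.

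**4. Effect on the test.** Assume no drug effect and 40 per group (the planned baclofen group, with a comparator of equal size). The exact probability that Pearson's chi-squared test rejects at two-sided 5%, found by summing over all pairs of binomial counts, is:

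| Window, current patients | Both groups have the shorter window (concurrent TAU) | Only the baclofen group has it (historical group at 12 weeks) |
|---|---|---|
| 12 weeks | 4.9% | 4.9% |
| 11 weeks | 5.2% | 6.0% |
| 10 weeks | 5.4% | 9.6% |

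In the last column, 4.8 of the 6.0 points and 9.1 of the 9.6 points are rejections in favour of baclofen.

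**5. Week 24 against the end of baclofen.**
- End at week 12 (Table 2 legend): 24 − 12 = 12 weeks, which is 3 months by the table's convention.
- End at week 15 (dosing rows): 24 − 15 = 9 weeks. Three months later would be week 27 (15 + 12), or week 28 counting 13 weeks.
- Patients who take up the optional further 3 months finish at about week 25 (12 + 13) to week 28 (15 + 13), after the week-24 visit.

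**The case against.** Several stronger readings are tempting, and the text does not support them.

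- **That the primary abstinence window has four origins.** It does not. All four apply only to the final follow-up; the 3-month point has two. Every passage that ties abstinence or relapse to an origin counts from after detoxification. The sentence that uses the start of detoxification lists craving, psychiatric and quality-of-life measures and does not name the Timeline Follow-back. The short window is an inference from the shared visit. That inference still stands, because Table 2 places the Timeline Follow-back at that visit.
- **That week 24 cannot be three months after baclofen ends.** It can, if the end is week 12 as the Table 2 legend has it. What the documents contain is two different ends.
- **That type I error against concurrent TAU rises to 6% or nearly 10%.** The Procedure section has both concurrent groups assessed identically, so their windows shift together. Those figures concern the historical comparison only.
- **That the final follow-up lacks an origin for the controls.** Table 2 gives that visit to the baclofen group alone, and the planned 6-month comparisons are within that group.

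It is also fair to say that some of the four origins nearly coincide. Baclofen is meant to start straight after detoxification, so the abstract's origin lies within about a week of T0. Constant hazard may overstate the effect, since the abstract describes relapse as often coming soon after detoxification; trimming the last weeks would then change the rate less. The article calls the study explorative. These arguments reduce the size of the problem but do not remove the conflict between the Procedure section and the Statistical analyses section.

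**Conclusion.** The point holds in a limited form. The 3-month visit has two conflicting origins, and following the Procedure section would leave the Timeline Follow-back short of the 3 months after detoxification that the analysis uses, with no later record for TAU-only patients. The shortfall equals the length of detoxification, which the documents do not state.

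The baclofen against concurrent TAU comparison keeps its error rate (5.2% to 5.4%). The historical comparison is exposed: 36% would become 39% or 43%, and type I error 6.0% or 9.6%, for a shortfall of 1 or 2 weeks. This assumes constant hazard, 40 per group, visits actually dated by the Procedure section, and historical data kept at the full interval. If centres follow Table 2, the bias does not arise.

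Separately, the final follow-up carries four origins, and the end of baclofen carries two dates three weeks apart. These need reconciling, but they do not bear on the 3-month primary comparison.

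**What to change.** 1. In the Procedure section, time the 3-month visit and the abstinence window as 12 weeks from T0 (end of detoxification) in the baclofen and TAU-only groups, in line with Table 2 and the Statistical analyses section.
2. Cut the historical data at the same interval after detoxification.
3. In the abstract and the Procedure section, state the 6-month follow-up as week 24 from T0, for the baclofen group only, as Table 2 has it. Claim no 24-week outcome for TAU-only or historical patients: Table 2 has no Timeline Follow-back for TAU at week 24, and the article does not say how long the historical group was followed.
4. Reconcile the Table 2 legend, the dosing rows and the text on when baclofen treatment ends. Which of them is right is for the sponsor to settle.

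Cost: the visit dates given to centres must be aligned as well as the wording. No new visits or instruments are needed. Step 2 assumes that the historical follow-up is recorded in enough detail to be cut at a chosen date, which the article does not say.
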